### ***Withdrawal criteria***

A patient may be removed from the study treatment for the following reasons; however, whenever possible the patient should be followed regardless of their protocol adherence as per the efficacy and safety evaluations:

- Patient withdraws consent or requests discontinuation from the study for any reason
- Termination of the study
- Lost to follow-up.
- Due to toxicity, depending on the severity and the relationship of the adverse event to the experimental therapy.

Patients who withdraw from this study or are lost to follow-up after signing the informed consent form (ICF) (or giving oral consent) and administration of the study product, will not be replaced. The reason for patient discontinuation from the study will be recorded on the appropriate case report form.

## **8. STUDY PROCEDURES AND ENDPOINTS**

### ***Study Procedures***

#### ***Informed Consent***

Patients with suspicion of COVID-19 pneumonia will be evaluated by the investigators at the participating sites. Oral consent will be accepted in order to avoid paper handling. Investigator must reflect the process of obtaining consent in the patient's clinical documentation. Written consent by patient or representatives will be obtained whenever possible.

#### ***Screening and Inclusion (Visit -1)***

Patients will be screened in the hospitalization ward by the investigators of the trial. Screening will take place within 1 day of selection, and administration of the first dose of sarilumab will be done within the following 24 hours. Screening will be preceded by a presentation of the complete information about the clinical study to the subject or family member by the investigator followed by signature of the informed consent form or by obtaining oral consent.

After the informed consent, all the following assessments are performed to determine eligibility requirements as specified in the inclusion and exclusion criteria and before the patient receives any study medication:

- Positive SARS-CoV-2 test result. Laboratory-confirmed SARS-CoV-2 infection as determined by PCR in naso/oropharyngeal swabs or any other relevant.

-Focused medical history, including the following information:

- Patient demographic characteristics: age, sex, race
- History of relevant chronic medical conditions and concomitant medications
- COVID-19 history: date of confirmation of disease, disease duration, fever, cough, other related symptoms.
- COVID-19 background medication: Corticosteroids, retrovirals, Hidroxychloroquine, etc.

-Focused physical examination: including vital signs, weight, auscultation, signs of respiratory distress, and any other as clinically indicated

-Oxygen supplement requirements: type and FiO2

-Oxygen parameters: SaO2, PaO2 (if available), SaO2 or PaO2/FiO2 Indexes

-Review recent radiographic imaging (x-ray or CT scan), valid up to 96h prior to randomisation.

-Laboratory disease parameters (IL-6, LDH, d-dimer, CRP, BUN, Ferritin, total white blood cell and total lymphocytes count, platelets count, and liver enzyme studies), valid within 24h prior to randomization

-Optional blood samples will be collected at baseline for future pharmacogenomic exploratory research\*

-Pregnancy Test (Pregnancy test in women of childbearing potential)

-Brescia-COVID Scale, CURB-65

-Adverse events

The overall eligibility of the subject to participate in the study will be assessed once all screening values are available. The screening process can be suspended prior to complete assessment at any time if exclusions are identified by the study team. Study subjects who qualify will be immediately randomized and treatment should be administered within 24 hours after randomization.

\*Optional blood samples for exploratory research. For patients agreeing to participate and signing the specific biobank informed consent, two additional blood samples will be collected at baseline:

- One yellow tube with gel (5 ml), to collect serum after centrifugation.
- One violet EDTA tube (5 mL) to collect plasma and Buffy Coat after centrifugation.

Specific details to collect and store these samples will be provided to all participating centers.

Note: the data of all the procedures carried out as part of the customary healthcare before the informed consent shall be recorded in the study and do not have to be repeated after the consent is given, if they are obtained in a time period of 48h.

### *Randomisation and Treatment*

Participants will be randomly assigned to:

-Treatment arm: sarilumab 200mg if <75kg body weight or 400mg if ≥75kg body weight, corticosteroids plus SOC for COVID-19

-Control arm: corticosteroids plus SOC for COVID-19.

Corticosteroids will be administered intravenously following this posology: Methylprednisolone 1mg/kg/day (or equivalent CS doses) for at least 3 days plus SOC according to local clinical practice protocols.

Study participants will be assigned using a central randomization service implemented in the eCRF. Randomization codes will be provided by the CRO and will be charged into the eCRF as to maintain the treatment concealment.

The following assessments will be performed before study drug administration to confirm selection criteria:

-Vital signs including SpO2 and Ta

-Focused physical examination: including vital signs, weight, auscultation, signs of respiratory distress, and any other as clinically indicated

-Oxygen supplement requirements: type and FiO2

-Oxygen parameters: SaO2, PaO2 (if available), SaO2 or PaO2/FiO2

#### *Efficacy assessments: follow up visits*

Clinical follow-up visits will be performed at 3, 5, and 15 days after treatment randomisation. Patients in SOC group without sarilumab progressing to severe respiratory failure fulfilling criteria for treatment with anti-IL6 inhibitors according to clinical practice guidelines, as defined by the presence of Brescia-COVID 2-3 plus inflammatory markers, will be rescued with sarilumab at the same doses and be included in an open-label phase. This group of patients will be followed up by two additional weeks after receiving sarilumab as rescue medication (days 3, 5 and 15 following sarilumab administration).

Patients randomly assigned to sarilumab therapy at baseline progressing to Brescia-COVID 2-3 will be rescued according to local clinical practice protocols.

For all patients a final follow-up visit is planned at D28 from randomization, regardless of the initial treatment assigned.

The following outcomes should be assessed:

- Hospitalization.
- ICU admission
- Hospital discharge
- Oxygen requirements.
  - Oxygen mask with reservoir bag.

- Non-invasive mechanical ventilation (via mask) or high flow oxygen nasal tubes
  - Mechanical ventilator requirement (via endotracheal tube or tracheostomy tub).
  - ECMO requirement.
- Ordinal scale score:
  1. Not hospitalized, no limitations on activities.
  2. Not hospitalized, limitation on activities.
  3. Hospitalized, not requiring supplemental oxygen.
  4. Hospitalized, requiring supplemental oxygen.
  5. Hospitalized, on non-invasive ventilation or high flow oxygen devices or oxygen mask with reservoir bag.
  6. Hospitalized, on invasive mechanical ventilation or ECMO.
  7. Death.
- PaO2/FiO2 Index or SpO2/FiO2 Index.
- Temperature °C
- Chest radiography (at least one during the follow-up period, recommended between D3-5, unless medically indicated any other day as part of the routine care)
- Laboratory disease parameters (CRP, d-dimer, IL-6, LDH, lymphocyte counts, ferritin, plus any routing laboratory determinations usually performed by the patients's physicians)
- Death.
- Concomitant medications
- Brescia-COVID score
- Adverse events: Adverse events (AEs), serious AEs, and laboratory abnormalities from the signature of the informed consent form or oral consent documentation, where appropriate. At inclusion they will be collected from the beginning of sarilumab administration. AEs will be documented as per the National Cancer Institute's Common Terminology Criteria for Adverse Events (CTCAE) version 5.0 (Appendix 4).

If the patient has been discharged, they will be contacted by phone. If possible, a visit will be scheduled to complete the evaluation.

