**To evaluate safety of sarilumab as compared to SOC**

Safety through day 29

- Cumulative incidence of serious adverse events (SAEs)
- Cumulative incidence of Grade 3 and 4 adverse events (AEs).

Serious adverse events (SAEs).  
Grade 3 or 4 Adverse events (AEs).

|                                                                                                                                                   |                                                                                                                                    |
|---------------------------------------------------------------------------------------------------------------------------------------------------|------------------------------------------------------------------------------------------------------------------------------------|
| To evaluate differences in the effect of sarilumab on the serum levels of inflammatory cytokines in patients infected with COVID-19.       | Changes in serum level of CRP, IL-6, lymphocyte count, neutrophils count, d-dimer, LDH, ferritin, coagulation tests                |
| To evaluate differences in the proportion of patients showing more than >1 organ failure, e.g. cardiovascular, liver and kidney failure | Patients showing more than >1 organ failure through day 15                                                                         |
| To identify prognosis factors of sarilumab efficacy related to laboratory parameters or disease features                                   | Focused medical history, demographic characteristics, COVID-19 history, concomitant medication, and laboratory disease parameters. |

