### ***Calendar of Evaluation of Trial Variables***

Safety will be evaluated through the collection of all AE for up to 28 days.

The Principal Investigator may decide to conduct interim analysis of study data at any time, even while some subjects may remain in follow-up. The timing of data analysis is the prerogative of the Principal Investigator, regardless of continuing long-term follow-up of study subjects.

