#### ***Registry of AE***

All AE will be documented, including the ones observed during clinical visits and the ones reported by the patient. AEs will be documented throughout the duration of the trial. The patient should be asked about possible AEs in the time between clinical visits.

All AE will be documented in the CRF and in the medical records.

All AE will be followed until resolution, until 15 days after the administration of the first dose of sarilumab (V1), or until toxicity is considered non-reversible or is grade 1.

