#### ***Procedure of notification***

##### ***Reporting of SAEs***

In case of occurrence of a SAE that must be reported to pharmacovigilance, a SAE Serious Adverse Events Reporting Form must be completed and signed by the investigator within 24 hours. The investigator will keep a copy of this SAE form on file at the study site.

When additional information about the SAE becomes available, or when the SAE is resolved, or when any change is unexpected, the investigator must provide further information in the form of a written narrative that should also be sent to pharmacovigilance. The responsible will review the received form and will ask for additional information if needed. In the event of SUSAR, follow-up information will be provided.

SAE appearing more than 15 days from the end of the experimental therapy will be reported if the investigator considers there is a causal relationship to the therapy or if it is of medical importance.

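### Adverse-event rules dated from a sarilumab dose conflict with the protocol's arm-neutral rules and, if applied to case report form data, could under-record late SAEs in the sarilumab arm only

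*Protocol*

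**What the plan says.** **Rules dated from the study drug**
- Section 8, Efficacy assessments, on the start of collection: "At inclusion they will be collected from the beginning of sarilumab administration".
- Section 9, Registry of AE: one of the alternative end points for following an AE is "until 15 days after the administration of the first dose of sarilumab (V1").
- Section 9, Reporting of SAEs: "SAE appearing more than 15 days from the end of the experimental therapy will be reported if the investigator considers there is a causal relationship". The sentence goes on to admit late SAEs of medical importance as well.

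Under Randomisation and Treatment, the control arm receives corticosteroids plus SOC. A control has a sarilumab date only if rescued. Table 3 labels that rescue visit V1, the same label as the baseline visit in Table 2.

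**Rules that do not depend on arm**
- The sentence just before the first quote above: "Adverse events (AEs), serious AEs, and laboratory abnormalities from the signature of the informed consent form or oral consent documentation, where appropriate".
- Registry of AE: "AEs will be documented throughout the duration of the trial".
- Calendar of Evaluation of Trial Variables: "Safety will be evaluated through the collection of all AE for up to 28 days".
- Table 2 schedules AE/SAE reporting from V1 to the day-28 visit, which section 8 counts from randomisation for all patients.

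**Planned use of the data**
- Table 1 compares safety with SOC by cumulative incidence of SAEs and of grade 3-4 AEs through day 29. The secondary endpoint list gives day 15 as the safety time frame.
- Section 10 includes adverse events in the inferential analyses and analyses binary safety outcomes like the primary endpoint.
- The Safety population requires receipt of the investigational product.

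**The concern.** A cumulative incidence can be compared between arms only if events are captured over the same time and by the same rule. Here three rules depend on a date that exists for one randomised arm and, in the other, only after rescue. The causality test has the same problem: Definitions has causality judged against sarilumab, so the test has no meaning for a control who never receives it. The trial is open-label, so in the sarilumab arm it is an unblinded judgement.

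If sites let the late-SAE rule decide what enters the case report form, unrelated late SAEs drop out of the sarilumab arm while controls are recorded to day 28. A binary analysis with no stated allowance for observation time would carry that straight into the risk ratio, in sarilumab's favour. Sites could also settle the conflict differently from one another.

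**Working it through.** **Inputs from the protocol.** 100 patients per arm; two-sided 5% level; dosing within 24 h of randomisation; late-SAE rule from 15 days after experimental therapy (a single infusion); final visit at day 28.

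**Assumed.** The protocol gives no SAE risk. I take a 28-day risk p of 10%, 20% or 30%, equal in both arms, so every difference below is artefact.

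**The plan's own figure.** For 25% v 10%, 80% power, pooled variance and no continuity correction: n = [1.960·√(2·0.175·0.825) + 0.842·√(0.25·0.75 + 0.10·0.90)]² / 0.15² = (1.053 + 0.443)² / 0.0225 ≈ 99.5, so 100 per arm (power 80.2%). The stated size reproduces. It is used here only for n.

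**Step 1: start clock.** With constant hazard h = −ln(1−p)/28, the risk recorded over d days is F(d) = 1 − exp(−h·d). Starting at the dose costs the sarilumab arm at most about one day after randomisation. For p = 20%, h = 0.00797 and F(27) = 19.4% v 20.0%, a ratio of 0.97. False rejection is 5.1% to 5.2% across the three risks. A two-day loss, if controls count from consent, gives ratios of 0.93 to 0.94 and 5.3% to 5.9%. Both are negligible.

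**Step 2: late-SAE rule, worst case.** Suppose every SAE after day 15 is lost in the sarilumab arm and none in controls. For p = 20%, F(15) = 1 − exp(−0.00797·15) = 11.3%, a gap of 8.7 points. The rejection probability is that of a two-proportion test with 100 per arm: Φ[(d − 1.96·s0)/s1] + Φ[(−d − 1.96·s0)/s1], with d = 0.0873, pooled standard error s0 = 0.0514 and unpooled s1 = 0.0510.

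| Assumed 28-day risk | Sarilumab, recorded | Control, recorded | Ratio | False rejection |
|---|---|---|---|---|
| 10% | 5.5% | 10.0% | 0.55 | 22% |
| 20% | 11.3% | 20.0% | 0.56 | 40% |
| 30% | 17.4% | 30.0% | 0.58 | 55% |

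**Step 3: front-loaded events.** With a Weibull hazard, F(15) = 1 − (1−p)^((15/28)^k). At p = 20%, k = 0.7 gives 13.4% and k = 0.5 gives 15.1%. At p = 30% they give 20.6% and 23.0%. The gap narrows when events come early.

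**Step 4: partial reporting.** If half of the late SAEs are still reported as medically important, the late hazard is halved and the 13 days after day 15 count as 6.5. At p = 20%, 1 − exp(−0.00797·21.5) = 15.7% v 20.0%, with about 12% false rejection.

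**Step 5: rescued controls.** For a control rescued on day r, the same rule would apply only after day 15 + r. From r = 13 onward it never applies within 28 days.

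**Step 6: when the effect vanishes.** If the rule governs only what is sent to pharmacovigilance, case report form data are unaffected. If the comparison stops at day 15, nothing restricted falls inside it.

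**The case against.** The strongest reply is that the protocol already gives both arms the same window. Collection starts at consent, AEs are documented throughout the trial and collected for up to 28 days, and Table 2 makes no distinction by arm. On this view an unrescued control does have a start date.

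Two of the three dose-dated rules are also weaker than they look. The 15-day limit in Registry of AE governs how long a recorded event is followed, not whether a new one is captured. The late-SAE rule sits under the notification procedure, which concerns the form sent to pharmacovigilance. The protocol separates the two elsewhere: deaths need not be reported as SAEs but are still entered in the CRF.

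Most of this stands. A reader might infer that the two arms are in fact observed over different windows and that the safety comparison is therefore biased. The documents do not support that, because the arm-neutral rules are equally explicit.

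What the reply does not remove is the contradiction. The protocol never says that the late-SAE rule is limited to notification, nor which start sentence prevails, and it gives three safety horizons. The common window is a reasonable reading, but not one the text secures.

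**Conclusion.** The point holds as a conflict between dose-dated and arm-neutral rules that can, on one reading, filter late SAEs in the sarilumab arm only. The conflict is certain; the bias is conditional. The bias needs the late-SAE rule to be applied to case report form data and the comparison to run beyond day 15. Its direction would then favour sarilumab.

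The 8.7-point gap and 40% false rejection at an assumed 20% risk are an upper bound, resting on constant hazard and total loss of late SAEs in one arm. They should not be read as the expected error. The start-clock difference alone does not matter.

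This affects a secondary objective of an exploratory phase II trial; the primary endpoint and sample size are untouched. It still deserves correction before data are collected, because late SAEs that were never entered may be hard to recover.

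**What to change.** - For the between-arm comparison, state one capture window for both arms, from randomisation (or consent) to the day-28 visit. Enter all SAEs and grade 3-4 AEs in the CRF without a causality filter.
- In Reporting of SAEs, say that the 15-day rule governs pharmacovigilance notification only.
- In Registry of AE and the section 8 adverse-event bullet, replace the sarilumab date with the common one.
- Align the horizon across Table 1 (day 29), the secondary endpoint list (day 15) and the Calendar of Evaluation (28 days).
- Describe events after rescue on a separate clock from the rescue dose, outside the randomised comparison.
- Make sure the safety comparison includes controls who never receive sarilumab. As worded, the Safety population (defined twice in section 10) leaves them out, and correcting the clocks alone would not bring them back.

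The cost is wording plus a few more late SAE entries. The day-28 AE/SAE visit is already in both schedules, and neither sample size nor treatment changes.

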#### *Follow-up period*

At any time during the study, the patient may be seen in clinic for a visit outside of the protocol-specified visit schedule. Selected tests as required may be performed at the discretion of the Investigator Team. The frequency of clinical visits could increase if deemed necessary because of clinical situation, incapacity or demands of the patient. In the event that a study subject leaves the study early (i.e., early termination) and additional visit will be obtained with additional testing as indicated at the discretion of the Principal Investigator.

The Principal Investigator may decide to conduct final analysis of study data at any time, even while some subjects may remain in long-term follow-up. This decision may also take place after all

study subjects have been completed the scheduled 28-day follow-up period for each patient. The timing of data analysis is the prerogative of the Principal Investigator, regardless of continuing long-term follow-up of study subjects.

CONFIDENTIAL

**Table 2. SCHEDULE OF ACTIVITIES (SOA)**

The parameters, clinical history, laboratory and instrumental data of patients will be collected according to the following scheme:

| Procedure                                                                             | V0             | V1                   | V2             | V3             | V4          | V4 Follow-up  |
|---------------------------------------------------------------------------------------|----------------|----------------------|----------------|----------------|-------------|---------------|
| Day (+/Window)                                                                        | Screening      | Baseline/ First dose | 72h            | 5 day          | 15 day (+2) | 28 day (+/-2) |
| Informed Consent                                                                      | X              |                      |                |                |             |               |
| Inclusion/exclusion criteria                                                          | X              | X                    |                |                |             |               |
| Demography and medical history                                                        | X              |                      |                |                |             |               |
| SARS-CoV-2 test                                                                       | X              |                      |                |                |             |               |
| COVID-19 history                                                                      | X              |                      |                |                |             |               |
| Rx Thorax                                                                             |                | X b       | X a | X a | X           |               |
| Randomization                                                                         |                | X                    |                |                |             |               |
| Study treatment administration                                                        |                | X                    |                |                |             |               |
| Concomitant medication                                                                |                | X                    | X              | X              | X           |               |
| Laboratory tests                                                                      |                | X c       | X              | X              | X           |               |
| Optional blood for exploratory studies                                                |                | X d       |                |                |             |               |
| Pregnancy Test                                                                        | X              |                      |                |                |             |               |
| PaO 2 /FiO 2 Index                                              |                | X                    | X              | X              | X           |               |
| Oxygen requirements, Oxygenation parameters (SaO 2 , arterial blood gases) |                | X                    | X              | X              | X           |               |
| Clinical data collection                                                              |                | X                    | X              | X              | X           | X             |
| Physical examination                                                                  | X              | X                    | X              | X              | X           |               |
| Laboratory tests                                                                      | X c | X c       | X              | X              | X           |               |
| Brescia-COVID score                                                                   | X              | X                    | X              | X              | X           |               |
| Vital signs: SpO 2 /T a                                         |                | X                    | X              | X              | X           |               |
| Mechanical ventilator requirement                                                     |                | X                    | X              | X              | X           |               |
| Mortality                                                                             |                |                      | X              | X              | X           | X             |
| AE /SAE reporting                                                                     |                | X                    | X              | X              | X           | X             |

a- At least one radiographic assessment will be conducted during the follow-up visits, initially scheduled at D3 visit or D5 visit, unless otherwise medically indicated

b- Valid any imagin available up to 96h prior to randomisation

c- A complete laboratory parameters assessment should be available within 24 hours prior to randomisation

d-An additional blood sample will be collected and stored at HUPH biobank for future studies

CONFIDENTIAL

**Table 3. SCHEDULE OF ACTIVITIES OPEN-LABEL RESCUE PHASE (SOA) (SOC group without sarilumab progressing to severe respiratory failure)**

The parameters, clinical history, laboratory and instrumental data of patients will be collected according to the following scheme:

| Procedure                                                                                                                                                                                   | V1                         | V2  | V3                | V4 F/Uf     | V5 follow up*                            |
|---------------------------------------------------------------------------------------------------------------------------------------------------------------------------------------------|----------------------------|-----|-------------------|-------------|------------------------------------------|
| Day (+/Window                                                                                                                                                                               | Sarilumab rescue treatment | 72h | 5 day ( $\pm 1$ ) | 15 day (+2) | 28-day (+/-2) from initial randomisation |
| Inclusion criteria (Patients in SOC group without sarilumab progressing to severe respiratory failure fulfilling as defined by the presence of BRESCIA-COVID 2-3 plus inflammatory markers) | X                          |     |                   |             |                                          |
| Rx Thorax                                                                                                                                                                                   | X                          |     |                   | X           |                                          |
| Sarilumab administration                                                                                                                                                                    | X                          |     |                   |             |                                          |
| Concomitant medication                                                                                                                                                                      | X                          | X   | X                 | X           |                                          |
| Laboratory disease parameters b                                                                                                                                                             | X                          | X   | X                 | X           |                                          |
| PaO 2 /FiO 2 Index                                                                                                                                                    | X                          | X   | X                 | X           |                                          |
| Oxygen requirements, Oxygenation parameters (SaO 2 , arterial blood gases)                                                                                                       | X                          | X   | X                 | X           |                                          |
| Clinical data collection                                                                                                                                                                    | X                          | X   | X                 | X           | X                                        |
| Physical examination                                                                                                                                                                        | X                          | X   | X                 | X           |                                          |
| Brescia-COVID Scale                                                                                                                                                                         | X                          | X   | X                 | X           |                                          |
| Vital signs: SpO 2 /T a                                                                                                                                               | X                          | X   | X                 | X           |                                          |
| Mechanical ventilator requirement                                                                                                                                                           | X                          | X   | X                 | X           |                                          |
| Mortality                                                                                                                                                                                   |                            | X   | X                 | X           | X                                        |
| AE /SAE reporting                                                                                                                                                                           | X                          | X   | X                 | X           | X                                        |

